### Outcome measures

#### Primary outcomes.

The repeated measures of the six domains of IC (cognitive decline, limited mobility [locomotor], malnutrition [Vitality], visual impairment, hearing loss, and depressive symptoms) are the primary outcomes of this study. These outcomes will be assessed at baseline and weeks 4, 8, and 12, using the WHO ICOPE screening tool. The ICOPE screening tool is a sensitive instrument to detect IC among community-dwelling older adults that does not require a substantial workforce [18]. It is used as the first step in each care pathway that covers all six core domains of IC to identify declines in IC across the six domains [19]. The psychometric properties of the ICOPE screening tools to assess IC domains among older persons from different settings have been reported in a few studies [20–22]. However, a systematic review found that the methods for assessing each of the IC domains differ substantially across studies and there is no consensus on the best method to compute an eventual global compound score to evaluate IC [23]. On the other hand, further improvements are needed in the vitality dimension of the ICOPE screening tool to enhance its sensitivity in identifying individuals at risk of malnutrition [24]. Hence, for this study, some measures of outcomes for the IC domains will be based on those validated in the Malaysian population.

We will use the validated Malay version of the Mini-Mental State Examination (MMSE) to measure cognitive function [25]. This tool includes items on orientation (5 points), registration (3 points), attention and calculation (5 points), recall (3 points), and language (9 points), with a maximum score of 30. A higher MMSE score indicates better cognitive function.

To assess locomotor or mobility function, we will use the Short Physical Performance Battery (SPPB) [26,27]. The SPPB comprises three components: gait speed (measured over 4 meters), lower limb strength (five-repetition chair rise), and static balance (side-by-side, semi-tandem, and tandem stands), with each component contributing up to 4 points. The total SPPB score ranges from 0 to 12, with higher scores indicating better locomotion.

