For vitality assessment in the ICOPE screening tool, we will use questions on unintended weight loss of more than 3 kg in the past three months and appetite loss. This study will employ the validated Malay version of the short-form Mini Nutritional Assessment (MNA) [28]. The MNA has a maximum score of 14, with higher scores indicating better nutritional status.

For hearing and vision assessments, we will follow previously reported procedures, using self-reported hearing and vision impairment [29]. Participants will be categorized as having total or severe loss (0 points), moderate loss (0.5 points), or normal to mild loss (1 point).

Psychological function, as indicated by depression level, will be assessed using the validated Malay short-form Geriatric Depression Scale (GDS-15) [30]. This scale consists of 15 items with “Yes” (1 point) and “No” (0 point) responses; a higher score indicates a greater level of depression.

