### Data analysis

All statistical analyses will be conducted using SPSS version 29, with a significance level set at p < 0.05. Data will first undergo cleaning and analysis in SPSS, where frequency distributions and graphical representations will be used to identify outliers and missing values. For normality testing of interval data, the Kolmogorov-Smirnov and Shapiro-Wilk tests will be applied. Descriptive analysis will be conducted for participants’ demographics and baseline characteristics to describe data using tables, averages, standard deviations, ranges, frequencies, and percentages. Where appropriate, statistical comparisons between the intervention and control groups will be conducted, utilizing the independent t-test for continuous data and the Chi-square test for categorical data.

To evaluate the intervention’s impact on the primary outcomes, a repeated measures ANOVA will be conducted after data collection, as the primary outcomes involve measurements at baseline, week 4, week 8 and week 12, to evaluate the significant effects of time, intervention, and their interaction. For the secondary outcomes which involve measurements at baseline and week 12, the paired-t-test will be performed to determine the impact of the intervention.

The non-parametric tests will be performed if the main outcomes are not normally distributed that include the Friedman test and Wilcoxon signed-ranked test for the primary and secondary outcomes, respectively.

In the event of missing data due to participant dropout or incomplete data collection, an intention-to-treat (ITT) analysis will be employed to maintain the validity of the randomization process. Missing data will be managed using appropriate imputation techniques, depending on its nature and extent. For continuous variables, multiple imputation methods will be applied, while for categorical variables, methods such as last observation carried forward (LOCF) may be used. Sensitivity analyses will also be performed to assess the robustness of the results to the assumptions about the missing data.

To ensure data privacy and confidentiality, hard-copy forms collected from participants will be stored securely. All datasets will be digitized and saved on password-protected laptops, with backup copies maintained on password-protected USB drives and external hard drives. Access to these datasets is restricted to the principal researcher.

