## Limitations and considerations

Several limitations should be noted in this study. First, this study will be conducted in a single state in the northern region of Malaysia, where the predominant members of PAWE are of Malay ethnicity. This limitation may restrict the generalization of the findings to other states in Malaysia. However, given Malaysia’s diversity in culture, ethnicity, and healthcare infrastructure, this limitation is unavoidable. We suggest that each state may need to adapt the proposed module for local suitability.

The second anticipated limitation could be related to participant adherence to the module’s activities. Older adults may experience challenges such as hearing or vision impairments that could impact their understanding and adherence to the study protocol. To address this, we will contact each participant weekly to remind them of their roles and set goals as outlined in the module.

Thirdly, although we have calculated the sample size based on a recommended formula, older adults may still have the potential to withdraw from the study due to multiple declines in IC domains, as noted in the literature. We hope that weekly mobile phone reminders will help reduce the attrition rate and encourage participants to stay motivated in achieving their goals and caring for themselves.

Fourthly, there are possible bias in self-reported answers, the study will use trusted and proven tools, keep participants’ identities private, and ask questions in a neutral way to encourage honest responses. Combining this data with other sources like interviews or observations will make the results more reliable, and using simple, clear language will help avoid confusion.

Fifthly, there may be a long-term challenge in ensuring participants compliance to the interventions and data collection. To mitigate this potential issue, the researchers will keep in touch with participants through updates and reminders via phone calls and WhatsApp mode. The participants will be ensured of flexible schedules, simple processes, and appreciation for encouraging and motivating their involvement.

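### LOCF is the only imputation method named for categorical variables; if the three-level hearing and vision primary outcomes are handled as categorical, it could hide decline among people who withdraw

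*Protocol article*

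**What the plan says.** The Data analysis section of the protocol article splits the handling of missing values by variable type. The rule for continuous variables is firm: "For continuous variables, multiple imputation methods will be applied". The rule for the rest is looser: "while for categorical variables, methods such as last observation carried forward (LOCF) may be used". The same paragraph invokes intention-to-treat, says the technique will depend on the kind and amount of missingness, and adds: "Sensitivity analyses will also be performed to assess the robustness of the results to the assumptions about the missing data". It does not say what those analyses are.

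The Primary outcomes section lists six domains, ending with "visual impairment, hearing loss, and depressive symptoms) are the primary outcomes of this study". On timing it says: "These outcomes will be assessed at baseline and weeks 4, 8, and 12". For hearing and vision, both self-reported, it says: "Participants will be categorized as having total or severe loss (0 points), moderate loss (0.5 points), or normal to mild loss (1 point".

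The Limitations and considerations section says that "older adults may still have the potential to withdraw from the study due to multiple declines in IC domains, as noted in the literature". It offers weekly phone reminders as mitigation.

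**The concern.** LOCF assumes that nothing changes after the last visit attended. The article itself names a route by which that assumption fails: people may leave because they are declining in the domains being measured. Someone who leaves before the decline is recorded is kept at the earlier level. For a person who leaves before week 4, that is the baseline level.

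The filled-in value is then analysed as if it had been seen, so the analysis behaves as though every participant had been followed to week 12.

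The arms also differ in burden. The intervention arm has weekly meetings for four weeks, a workbook, exercises and goals; the control arm has one session. Dropout could therefore differ between arms, in either direction, and the arm that loses more decliners would look better than it is. Two of the six primary domains could be affected.

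**Working it through.** **1. Which rule governs hearing and vision.** Participants are placed in three levels, which points to the categorical rule. But the levels carry scores of 0, 0.5 and 1, and the Data analysis section applies repeated measures ANOVA to all primary outcomes, which points to the continuous rule. The text does not settle it, so what follows is conditional on the categorical reading.

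**2. The plan's allowance for loss.** The Sample size determination section raises 60 by about 15 to 20% and arrives at 70.
- As a multiplier: 60 × 1.15 = 69 and 60 × 1.20 = 72.
- As a divisor: 60/0.85 = 70.6, rounded up to 71, and 60/0.80 = 75.
- The stated 70 adds 10 people: 10/60 = 16.7% of the base, or 10/70 = 14.3% of those randomised.

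So the plan leaves room to lose 10 of 70, or 5 of 35 per arm if split evenly.

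**3. Bias of LOCF.** Let *d* be the share of an arm that drops out, and *δ* the mean fall in score after the last recorded visit among those people. Then

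LOCF mean − true week-12 mean = *d* × *δ*

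and the bias in the difference between two arms is *d*₁*δ*₁ − *d*₂*δ*₂.

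The documents give no rates of change for hearing or vision, so *δ* is an assumption. One level is 0.5 points, so *δ* = 0.25 to 0.5 means that between half and all of the dropouts fall one level unseen.

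| Dropout, arm 1 / arm 2 | Overstatement, arm 1 | Overstatement, arm 2 | Bias in favour of arm 1 |
|---|---|---|---|
| 14.3% / 14.3% | 0.036 to 0.071 | 0.036 to 0.071 | 0 |
| 20% / 20% | 0.05 to 0.10 | 0.05 to 0.10 | 0 |
| 20% / 10% | 0.05 to 0.10 | 0.025 to 0.05 | 0.025 to 0.05 |
| 30% / 10% | 0.075 to 0.15 | 0.025 to 0.05 | 0.05 to 0.10 |

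For example, at 20% against 10% with *δ* = 0.5: 0.20 × 0.5 − 0.10 × 0.5 = 0.05. The bias is proportional to *δ*, so a smaller unseen fall shrinks every entry in step. A decline already recorded at week 4 or 8 is carried forward as a decline and adds nothing to *δ*.

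**4. Effect on the error rate.** Simulation with no true effect, 4,000 trials per setting. Assumptions: 35 per arm; baseline shares of 5%, 20% and 75% for scores 0, 0.5 and 1; 30% fall one level; decliners four times as likely to drop out; baseline carried forward; arms compared at week 12 by t-test.

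| Dropout, arm 1 / arm 2 | Mean bias towards arm 1 | Type I error with LOCF |
|---|---|---|
| 15% / 15% | about 0 | 4.6% |
| 20% / 10% | 0.029 | 6.7% |
| 30% / 10% | 0.060 | 11.7% |

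With complete data the error rate was about 5% in each setting. Swapping the arms gave the mirror image. These inputs are severe for LOCF: every dropout leaves before week 4, and 30% decline within 12 weeks exceeds the 17.9% (vision) and 14.4% (hearing) impairment prevalence cited in the Introduction.

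**5. Uncertainty.** If 5 of 35 are lost per arm, a standard error based on 30 observed is √(35/30) = 1.08 times one based on 35. As a rough guide, treating filled-in values as observed understates the standard error by up to that order at the plan's own level of loss. The simulation with equal dropout shows that this alone did not raise the false-positive rate; that came from imbalance between arms.

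**The case against.** The strongest reply is that the plan does not commit to LOCF. The wording is permissive, the technique is to depend on the missingness found, and sensitivity analyses on the missing-data assumptions are already promised. What remains is that LOCF is the only method offered for this class of variable, and sensitivity analyses of unstated content do not repair a weak primary method.

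Second, a reader might infer that two primary outcomes are certain to be analysed under LOCF. The documents do not support that: the numeric scores and the ANOVA for all primary outcomes allow them to be treated as continuous and multiply imputed. That objection stands, and the point is therefore conditional.

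Third, a reader might infer that the plan expects decliners to leave. It says only that they may, across several IC domains rather than hearing or vision in particular, and it offers a mitigation. Few level changes are likely in 12 weeks in any case: blindness and deafness are excluded, and normal and mild loss share one level. This limits the likely size but does not make carrying forward a sound assumption.

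Fourth, a reader might infer that LOCF invalidates the intention-to-treat analysis. It does not, since everyone stays in the randomised arm; the problem is possible bias and understated uncertainty.

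Last, standard multiple imputation assumes missing at random, so it does not by itself cure dropout driven by unseen decline. That is correct, and it is why the fix needs a second part.

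**Conclusion.** The point holds in a limited form. LOCF is a poor method to name for categorical variables in a trial whose protocol accepts that withdrawal may follow decline in the measured domains. If hearing and vision are handled as categorical, LOCF can bias the comparison towards the arm that loses more unrecorded decliners and makes the data look more complete than they are.

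The documents do not allow the size to be derived. If dropout and unseen decline are equal across arms, there is little or no bias between them. If they differ, the illustrations give 0.025 to 0.05 points at 20% against 10% dropout and 0.05 to 0.10 at 30% against 10%, on a 0–1 score. They rest on assumed declines that are probably high for 12 weeks. A reader might take one of these figures as the expected false benefit of PTICOPE. The documents support neither a particular figure nor a direction.

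This is a weakness in at most two of six primary domains, worth correcting because the correction is cheap. It does not threaten the trial as a whole.

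**What to change.** In the Data analysis section:
- Delete LOCF.
- State that missing hearing and vision values are handled by multiple imputation suited to ordered categories, for example ordinal logistic imputation or predictive mean matching. Use arm, baseline and the observed visits of that outcome as predictors. With 70 participants and probably few in the lowest level, the model should stay this small.
- Define one of the sensitivity analyses already planned as missing-not-at-random: shift the imputed values of dropouts downwards over a stated range, including different shifts in the two arms, and report where the conclusion changes. This is needed because multiple imputation itself assumes missing at random.

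The cost is a few sentences, slightly more analysis work and possibly wider intervals. No data collection changes. Because the section commits all analyses to SPSS version 29, the team should confirm that both steps can be run there or name a second package.

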### Ethics and dissemination

Ethical approval was obtained from the UiTM Research Ethics Committee (REC/09/2024 (PG/MR/437)), and this study is registered as a clinical trial in the Thai Clinical Trial Registry TCTR20241029007) (https://www.thaiclinicaltrials.org/show/TCTR20241029007). Informed consent will be obtained from all participants, ensuring their privacy and right to withdraw at any time.

This study will adhere to ethical standards throughout all procedures. During participant recruitment, trained research assistants will meet with potential participants to explain the study’s purpose, procedures, benefits, potential risks, and participants’ right to withdraw at any time without consequences. Participants will have sufficient time to discuss any questions before signing the consent form. All data collected will be stored centrally, kept confidential, and anonymized. Data analysis will be conducted by the research team and used solely for study purposes within the research team.

Study findings will be submitted for publication in a peer-reviewed journal and presented at a relevant conference, such as the Asian Conference for Frailty and Sarcopenia, held annually in the region. The findings will support the proposal of a new physiotherapy approach based on PTICOPE for community-dwelling older adults.

## Discussion

The purpose of this study is to develop and evaluate the PTICOPE module, a Physiotherapy-led, WHO-ICOPE-based, person-centered integrated care program specifically tailored for older adults in Malaysia. This module aims to enhance intrinsic capacity across six key domains, namely, locomotor, vitality, psychological, cognitive, vision, and hearing, addressing unique cultural and healthcare access challenges faced by Malaysian older adults. By incorporating comprehensive exercises, goal-setting, advice, and regular monitoring, the PTICOPE module seeks to empower older adults to maintain and improve functional abilities and overall well-being within a community-based setting, thereby contributing to improved quality of life and reduced healthcare burden among the aging population.

The current PTICOPE module which is led by physiotherapists may be different from those that have been published such as the AMICOPE [12], INSPIRE ICOPE-CARE [13], and VIVIFRAIL [14], that were conducted in Spain, France, and tertiary hospitals in Spain, respectively. These differences in terms of language, socioeconomic factors, diet, lifestyles, and healthcare policy highlight the need to design specific interventions for integrated care to older adults. As far as we know, this is the first study using the constructs of the HBM to develop the features of the PTICOPE module. The applicability of the HBM constructs has been evident in several studies involving older persons with different conditions [32,33]. Nevertheless, the effectiveness of this application in the current study is yet to be ascertained once the study is completed. We also anticipate several challenges in the application of the HBM in the older population due to variations in their physical and psychological well-being.

It is also pertinent that the development of intervention to enhance IC is acceptable by the local community as one template may not apply to all due to the diverse world population of aging. This is evidenced by IC studies reported in several countries. For instance, a study reported in China and Japan revealed that IC decline is associated with social fragility and not modifiable factors [34]. In contrast, another study in China found poor self-rated health, multiple chronic conditions, recent falls, frequent physical pain, recent outpatient visits, hospitalizations, and pessimistic life expectancy were highly associated with IC decline [35]. While, a study conducted in India found age, gender, and smoking were related to IC decline [36]. These findings indicate that factors contributing to IC decline may differ across countries probably due to diversity in socioeconomic status, cultural norms, and healthcare policy, hence, may require different approaches in the personalized and integrated care pathways.

The development of the PTICOPE ensures a comprehensive review from expert panels who have at least 5 years of working experience with older adults, ensuring a strong understanding of the needs of older adults. Furthermore, older adults are also involved in the development of the module, in the face validation stage, to ensure that the module is acceptable to the study participants and effective in enhancing the well-being of the study participants.

## Strengths of the study

We would like to highlight several strengths of this proposed study. First, we will ensure that the development of the PTICOPE module involves expert review from all disciplines involved in or relevant to the care of older adults, including experienced physiotherapists, occupational therapists, and geriatricians, among others. The module’s development is based on the WHO framework and current literature, followed by content and face validation to ensure it effectively covers all aspects of IC.

## Limitations and considerations

Several limitations should be noted in this study. First, this study will be conducted in a single state in the northern region of Malaysia, where the predominant members of PAWE are of Malay ethnicity. This limitation may restrict the generalization of the findings to other states in Malaysia. However, given Malaysia’s diversity in culture, ethnicity, and healthcare infrastructure, this limitation is unavoidable. We suggest that each state may need to adapt the proposed module for local suitability.

The second anticipated limitation could be related to participant adherence to the module’s activities. Older adults may experience challenges such as hearing or vision impairments that could impact their understanding and adherence to the study protocol. To address this, we will contact each participant weekly to remind them of their roles and set goals as outlined in the module.

Thirdly, although we have calculated the sample size based on a recommended formula, older adults may still have the potential to withdraw from the study due to multiple declines in IC domains, as noted in the literature. We hope that weekly mobile phone reminders will help reduce the attrition rate and encourage participants to stay motivated in achieving their goals and caring for themselves.

Fourthly, there are possible bias in self-reported answers, the study will use trusted and proven tools, keep participants’ identities private, and ask questions in a neutral way to encourage honest responses. Combining this data with other sources like interviews or observations will make the results more reliable, and using simple, clear language will help avoid confusion.

Fifthly, there may be a long-term challenge in ensuring participants compliance to the interventions and data collection. To mitigate this potential issue, the researchers will keep in touch with participants through updates and reminders via phone calls and WhatsApp mode. The participants will be ensured of flexible schedules, simple processes, and appreciation for encouraging and motivating their involvement.

The participants fidelity and acceptability of the intervention will be ensured by regularly asking the understanding of the participants towards the PTICOPE module, regularly tracking their completed task, and gathering feedback during the follow-up sessions. Participants will be informed of their performance and goal-achievement that should be consistent with their exercise recording table during follow-ups to continue motivating them and strive for a better results and satisfaction.

